**4.1 Assessment of Causality**

Every effort should be made by the investigator to explain each adverse event and assess its relationship, if any, to study drug treatment. Causality should be assessed using the following categories: no (not related), or yes (reasonable possibility).

The degree of certainty with which an adverse experience is attributed to drug treatment (or alternative causes, e.g. natural history of the underlying diseases, concomitant therapy, etc.) will be determined by how well the experience can be understood in terms of the following:

**·** Known pharmacology of the drug

**·** Reaction of similar nature being previously observed with this drug or class of drug

**·** The event having often been reported in literature for similar drugs as drug related (e.g. skin rashes, blood dyscrasia)

**·** The event being related by time to drug administration terminating with drug withdrawal (dechallenge) or reproduced on rechallenge.

The investigator may change his/her opinion of causality in light of follow-up information, amending the SAE form. The causality assessment is one of the criteria used when determining regulatory reporting requirements.

## 4.2 Following-up of Adverse Events

Investigators should follow-up subjects with adverse events until the event has subsided (disappeared) or until the condition has stabilized.

### 4.3 Definition of Serious Adverse Events

A serious adverse experience is any event which is fatal, life threatening, disabling or incapacitating or results in hospitalization, prolongs a hospital stay or is associated with congenital abnormality. In addition, any experience which the investigator regards as serious or which would suggest any significant hazard, contraindication, side effect or precaution that may be associated with the use of the drug should be reported as a serious adverse event. Examples of such events are invasive or malignant cancers, intensive treatment in an emergency room or at home for allergic bronchospasm, blood dyscrasias or convulsions that do not result in hospitalization, or development of drug dependency or drug abuse.

Abnormal laboratory findings (e.g., clinical chemistry, hematology) or other abnormal

assessments (e.g., x-rays, scans, vital signs, etc.) that are judged by the investigator as

**clinically significant** will be recorded as AEs or SAEs if they meet the definition of an

AE or SAE.

**4.3.1 Life threatening definition**

An adverse event is life threatening if the patient was at immediate risk of death from the event as it occurred (i.e. it does not include a reaction that if it had occurred in a more serious form might have caused death). For example, drug-induced hepatitis that resolved without evidence of hepatic failure would not be considered life threatening even though drug-induced hepatitis could be fatal.

**4.3.2 Disability/incapacitating definition**

An adverse experience is incapacitating or disabling if the experience results in a substantial and/or permanent disruption of the patient's ability to carry out normal life functions.

**4.3.3 Hospitalization definition**

Hospitalization for elective treatment of a pre-existing condition that did not worsen from baseline is not considered an AE.

**4.3.4 Additional SAE definitions**

- All Grade 4 laboratory abnormalities

- Cardiovascular events have been seen in subjects taking other compounds that inhibit ErbB2 when used in combination with or following anthracyclines and interstitial pneumonitis has been reported in subjects taking compounds that inhibit ErbB1. As a precaution, the following will be reported as a SAE:

Cardiac dysfunction will be reported as an SAE and will be defined as any signs or symptoms of deterioration in left ventricular cardiac function that are Grade 3 (NCI CTCAE) or a **>**20% decrease in left ventricular cardiac ejection fraction relative to baseline, which is below the institution's lower limit of normal. Refer to NCI CTCAE grading of left ventricular cardiac function.

Subjects who have a **>**20% decrease in left ventricular cardiac ejection fraction relative to baseline, and the ejection fraction is below the institution's lower limit of normal, should have a repeat evaluation of ejection fraction 1-2 weeks later while still receiving investigational product (lapatinib). If the repeat ejection fraction evaluation confirms a **>**20% decrease in left ventricular cardiac ejection fraction, and the ejection fraction is below the institution's lower limit of normal, then investigational product should be temporarily discontinued. If the left ventricular ejection fraction recovers during the next 3 weeks, after consultation and approval of the medical monitor, the subject may be restarted on investigational product (lapatinib) at a reduced dose. For such subjects, monitoring of left ventricular ejection fraction will then be performed 2 weeks and 4 weeks after re-challenge and then every 4 weeks, thereafter. If repeat ejection fraction evaluation still shows a decrease **>**20% in left ventricular ejection fraction relative to baseline, and the value is below the institution's lower limit of normal, then the subject should be withdrawn from investigational product (lapatinib).

- Any signs or symptoms of pneumonitis that are >Grade 3 (NCI CTCAE) (defined as radiographic changes and requiring oxygen). Refer to NCI CTCAE grading of pneumonitis/pulmonary infiltrates.

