#### Guideline for dispersing whole lapatinib tablets

The following procedure is recommended for administering dispersed whole tablet(s) to patients who are unable to swallow:

Place ½ cup (120mL) of water in a glass container, then add six 250 mg lapatinib tablets to the container. Cover the container, let it stand for 5 minutes, and then stir the mixture intermittently for 10-20 minutes or until it is fully dispersed. Stir the container for 5 seconds then administer. Rinse the container with a ¼ cup (60mL) aliquot of water and administer (total of ¾ cup, 180mL of liquid is dispensed).

1. Lapatinib dose interruption/reduction

See section 3.5 - Management of Toxicity

####

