## 3.5 Management of Toxicity

**3.5.1 Criteria for Evaluating Cardiac and Respiratory Events**

**3.5.1.1 Asymptomatic Events**

Subjects who have a ≥ 20% decrease in left ventricular cardiac ejection fraction (LVEF) relative to baseline, and the LVEF is below the institution's lower limit of normal, should have a repeat evaluation of ejection fraction 1-2 weeks later while still receiving investigational product.

If the repeat ejection fraction evaluation confirms a ≥ 20% decrease in LVEF relative to baseline, and the ejection fraction is below the institution's lower limit of normal, then investigational product should be temporarily discontinued.

If the LVEF recovers during the next 3 weeks, after consultation and approval by the GSK Medical Monitor, the subject may be restarted on study treatment at a reduced dose. For such subjects, monitoring of LVEF will then be performed 2 weeks and 4 weeks after re-challenge, and then every 4 weeks thereafter.

If repeat ejection fraction evaluation still shows a decrease ≥ 20% in LVEF relative to baseline and the value is below the institution's lower limit of normal, then the subject should be withdrawn from investigational product. Ejection fraction should continue to be monitored every 4 weeks for at least 16 weeks or until resolution.

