**3.5.1.2 Symptomatic cardiac events**

**Subjects with an NCI CTCAE Grade 3 or 4 left ventricular systolic dysfunction or interstitial pneumonitis must be withdrawn from therapy.**

Note: Copies of echocardiograms and/or MUGA scans performed on subjects who experience a ≥ 20% decrease in LVEF relative to baseline (asymptomatic or symptomatic), and a cardiac ejection fraction is below the institution's lower limit of normal, will be required by GSK for review by an independent board. A ≥ 20% relative decrease from baseline in LVEF (asymptomatic or symptomatic), that is below the institution’s lower limit of normal is considered an SAE and must be reported to GSK.

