**3.6.1 Dose Delays and Dose Reductions**

Treatment may be delayed, up to 2 weeks, to allow for resolution of toxicity except in the event of NCI CTCAE Grade 3 or 4 left ventricular cardiac dysfunction or NCI CTCAE Grade 3 or 4 interstitial pneumonitis. The Investigator must consult the GSK Medical Monitor prior to continuing therapy for any subject requiring a delay of more than 2 weeks for unresolved toxicity, but in general, such subjects should be withdrawn from the study. If treatment is delayed for reasons other than toxicity (i.e., unplanned travel or vacation, or lack of transportation to the site) and the subject has insufficient investigational product available, the subject should resume the usual dosing schedule once drug supply has been made available. However, if the subject has been off therapy for more than 2 weeks, the Investigator must consult the GSK Medical Monitor prior to continuing therapy.

Dose reduction for drug-related toxicity is permitted; however the GSK Medical Monitor must be consulted prior to implementing any change in dosing. Only one dose reduction is permitted per subject and subjects should not be rechallenged to a higher dose level. If a NCI CTCAE Grade 3 or 4 drug-related event (other than left ventricular cardiac dysfunction or interstitial pneumonitis) has occurred, the investigator may discuss with the GSK Medical Monitor whether a reduction of dose is appropriate.

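### Section 4.3.4 keeps every patient with a qualifying LVEF fall on lapatinib until a rescan, which contradicts the mandatory withdrawal for Grade 3-4 left ventricular dysfunction in section 3.5.1.2

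*Protocol*

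**What the plan says.** Four parts of the protocol govern dosing after a cardiac event.

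- **Section 3.5.1.1**, headed as covering asymptomatic events. It applies when LVEF has dropped by at least 20% relative to baseline and is subnormal by the local standard. Its instruction is that such patients "should have a repeat evaluation of ejection fraction 1-2 weeks later while still receiving investigational product". Once the fall is confirmed, lapatinib is held. If LVEF recovers within 3 weeks and the medical monitor approves, it may be restarted at a reduced dose. Otherwise the patient is withdrawn.
- **Section 3.5.1.2**, headed as covering symptomatic cardiac events: "Subjects with an NCI CTCAE Grade 3 or 4 left ventricular systolic dysfunction or interstitial pneumonitis must be withdrawn from therapy". Its note, which makes the LVEF fall a reportable SAE, describes that fall as a "relative decrease from baseline in LVEF (asymptomatic or symptomatic), that is below the" institutional lower limit.
- **Section 3.6.1** permits a two-week treatment delay, but its wording is "to allow for resolution of toxicity except in the event of NCI CTCAE Grade 3 or 4 left ventricular cardiac dysfunction"; pneumonitis of those grades is excluded in the same way. The dose-reduction option is likewise worded to leave this event out: "If a NCI CTCAE Grade 3 or 4 drug-related event (other than left ventricular cardiac dysfunction or interstitial pneumonitis) has occurred".
- **Section 4.3.4**, among the additional SAE definitions. It defines cardiac dysfunction by two alternatives, Grade 3 signs or symptoms or the LVEF fall. It then says that patients with the LVEF fall "should have a repeat evaluation of ejection fraction 1-2 weeks later while still receiving investigational product (lapatinib"), and that after a hold and recovery "the subject may be restarted on investigational product (lapatinib) at a reduced dose".

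Section 3.4.1.1 sends the reader elsewhere for dose interruption and reduction: "See section 3.5 - Management of Toxicity".

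**The concern.** Section 4.3.4 gives dosing instructions of its own. It repeats the sequence of 3.5.1.1 for everyone with the qualifying LVEF fall, without the asymptomatic limit, without an exception for Grade 3-4 dysfunction and without a reference to 3.5.1. An investigator dealing with a cardiac SAE has good reason to open this section, because SAEs must be reported within 24 hours (section 4.4.1).

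The stake is patient safety only. On a literal reading of 4.3.4, a patient with Grade 3-4 left ventricular dysfunction stays on the suspect drug until the rescan and may later be rechallenged, although 3.5.1.2 requires withdrawal. The CTC count endpoint and its analysis are not touched.

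**Working it through.** **1. Can one patient fall under both rules?** Yes, on the protocol's own terms. The note in 3.5.1.2 says the LVEF criterion may be met with or without symptoms. The LVEF subsection of 1.3.3.2 reports four symptomatic decreases on lapatinib monotherapy, with dyspnea and cardiac failure, or palpitations.

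**2. What does each section order for that patient?** Take a patient with the qualifying LVEF fall and Grade 3-4 left ventricular dysfunction.

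| Step | 3.5.1.2 | 3.6.1 | 4.3.4 |
| --- | --- | --- | --- |
| Fall detected | Withdraw | Event excluded from toxicity delays | Continue dosing, rescan in 1-2 weeks |
| Fall confirmed | Already withdrawn | – | Hold |
| Recovery within 3 weeks | No restart provided | Event excluded from the Grade 3-4 dose-reduction option | Restart at a reduced dose if the medical monitor approves |

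The first and last columns cannot both be followed. Section 3.6.1 does not itself order withdrawal, but its two exclusions fit 3.5.1.2 and not 4.3.4.

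**3. Where is there no conflict?** For asymptomatic patients below Grade 3, sections 3.5.1.1 and 4.3.4 agree. For symptoms below Grade 3, no section requires withdrawal, so the point does not extend to them. The threshold prints as ≥ 20% in 3.5.1.1 and > 20% in 4.3.4; this may come from text conversion and plays no part here.

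**4. How often might it arise?** The inputs come from 1.3.3.2.1 and the LVEF subsection: about 3147 subjects treated with lapatinib; 41 with a decrease meeting the serious definition; of these, 36 asymptomatic, 4 symptomatic and 1 of unclear symptom status (36 + 4 + 1 = 41). Planned sample: 20. Assumption: programme-wide incidence applies to this trial.

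- The protocol's own figure: 41/3147 = 1.30%, which reproduces the stated 1.3%. Expected in 20 patients: 20 × 0.0130 = 0.26. The serious definition is either Grade 3-4 dysfunction or the LVEF fall, so 0.26 is an upper figure for cases meeting the LVEF criterion.
- Symptomatic, any grade: 4/3147 = 0.127%. Expected: 20 × 0.00127 = 0.025. The exact (Clopper-Pearson) 95% interval for the rate is 0.035% to 0.325%, or 0.007 to 0.065 cases in 20. Chance of at least one: 1 − (1 − 0.00127)^20 = 2.5%.
- Counting the unclear case: 5/3147 = 0.159%. Expected: 0.032. Chance of at least one: 3.1%.

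Grades are not reported for the symptomatic cases, so the Grade 3-4 share cannot be computed. All four were on monotherapy, which is this trial's regimen, but no monotherapy denominator is given, so no monotherapy rate can be formed.

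**5. What is the exposure for an affected patient?** Once-daily dosing for 1 to 2 weeks is 7 to 14 further doses before the hold.

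**The case against.** The strongest reply is that the protocol already contains the right rule in a stronger form. Section 3.5.1.2 says *must*, while 4.3.4 says *should*. Section 3.4.1.1 directs dose changes to 3.5, and 3.6.1 twice sets Grade 3-4 left ventricular dysfunction apart. Section 4 concerns reporting. The algorithm in 4.3.4 picks up only the LVEF alternative of its definition, so Grade 3 dysfunction may be read as left to 3.5.1.2. There are also other safeguards: the investigator may stop treatment for safety at any time (3.3.3.1), the SAE reaches the drug supplier within 24 hours (4.4.1), the scans go to an independent board (3.5.1.2), and a restart needs medical monitor approval.

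Most of this stands. It makes withdrawal the likelier outcome, and the 7 to 14 doses are what the literal text produces, not a forecast. The frequency figures also describe a wider group than the one in conflict.

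It does not remove the defect. No sentence ranks the sections. The asymptomatic limit sits only in the heading of 3.5.1.1, and the table of contents even lists that section as covering symptomatic events. A patient who meets both alternatives of the 4.3.4 definition falls within its instruction as written. A stopping rule for serious cardiac toxicity should not depend on the reader weighing *must* against *should* across two chapters.

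**Conclusion.** The concern holds. For a patient with both the qualifying LVEF fall and Grade 3-4 left ventricular dysfunction, 4.3.4 and 3.5.1.2 give incompatible dosing instructions, and 4.3.4 gives the wrong one. The contradiction rests on the text alone and needs none of the incidence figures.

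Severity is minor. On the assumption that programme-wide rates carry over, about 0.025 symptomatic cases of any grade are expected in 20 patients (0.007 to 0.065), or 0.032 with the unclear case. The group in conflict is an unknown part of these if, as the heading of 3.5.1.2 implies, Grade 3-4 cases are symptomatic.

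**What to change.** Delete the management paragraph from 4.3.4 and refer to 3.5.1 for dosing after a cardiac event, so that the rule stands in one place.

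If the paragraph is to stay, limit it to asymptomatic decreases and add that a patient with Grade 3 or 4 left ventricular dysfunction is withdrawn at once under 3.5.1.2, with no rescan on drug and no rechallenge.

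Either option is a one-paragraph wording amendment. It adds no assessments.

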### 4.4 Reporting Serious Adverse Events

Any serious adverse events which occur during the clinical study or within 30 days of receiving the last dose of study medication, whether or not related to the study drug, must be reported by the investigator. In addition, any SAEs which occur as a result of protocol specific diagnostic procedures or interventions must also be reported.

## 4.4.1 Lack of Efficacy

“Lack of efficacy” *per se* will not be reported as an AE. The signs and symptoms or clinical sequelae resulting from lack of efficacy will be reported if they fulfil the AE or SAE definition (including clarifications).

**All serious adverse events, in addition to being reported to the regulatory body and approving ethics committee by the investigator, must be reported by facsimile within 24 hours to GlaxoSmithKline.**

**< >**

**< >**

The SAE report should comprise a full written summary, detailing relevant aspects of the adverse events in question. Where applicable, information from relevant hospital case records and autopsy reports should be included. Follow-up information should be forwarded to GSK within 24 hours.

SAEs brought to the attention of the investigator at any time after cessation of lapatinib and considered by the investigator to be related or possibly related to lapatinib must be reported to GSK if and when they occur. Additionally, in order to fulfil international reporting obligations, SAEs that are related to study participation (e.g., procedures, invasive tests, change from existing therapy) or are related to a concurrent medication will be collected and recorded from the time the subject consents to participate in the study until he/she is discharged.

## 4.5 Pregnancy

Patients who become pregnant during the study should discontinue the study immediately.

Patients should be instructed to notify the investigator if it is determined after completion of the study that they become pregnant either during the treatment phase of the study or within five days after the treatment period.

Whenever possible a pregnancy should be followed to term, any premature termination reported, and the status of the mother and child should be reported to GlaxoSmithKline after delivery.

**Appendix A World Medical Association Declaration of Helsinki**

Recommendations guiding physicians in biomedical research involving human subjects

Adopted by the 18th World Medical Assembly

Helsinki, Finland, June 1964

and amended by the

29th World Medical Assembly

Tokyo, Japan, October 1975

35th World Medical Assembly

Venice, Italy, October 1983

41st World Medical Assembly

Hong Kong, September 1989

and the

48th General Assembly

Somerset West, Republic of South Africa, October 1996

**INTRODUCTION**

It is the mission of the physician to safeguard the health of the people. His or her knowledge and conscience are dedicated to the fulfilment of this mission.

The Declaration of Geneva of the World Medical Association binds the physician with the words, “The health of my subject will be my first consideration,” and the International Code of Medical Ethics declares that, “A physician shall act only in the subject’s interest when providing medical care which might have the effect of weakening the physical and mental condition of the subject.”

The purpose of biomedical research involving human subjects must be to improve diagnostic, therapeutic and prophylactic procedures and the understanding of the etiology and pathogenesis of disease.

In current medical practice most diagnostic, therapeutic or prophylactic procedures involve hazards. This applies especially to biomedical research.

Medical progress is based on research which ultimately must rest in part on experimentation involving human subjects.

In the field of biomedical research a fundamental distinction must be recognized between medical research in which the aim is essentially diagnostic or therapeutic for a subject, and medical research, the essential object of which is purely scientific and without implying direct diagnostic or therapeutic value to the person subjected to the research.

Special caution must be exercised in the conduct of research which may affect the environment, and the welfare of animals used for research must be respected

Because it is essential that the results of laboratory experiments be applied to human beings to further scientific knowledge and to help suffering humanity, the World Medical Association has prepared the following recommendations as a guide to every physician in biomedical research involving human subjects. They should be kept under review in the future. It must be stressed that the standards as drafted are only a guide to physicians all over the world. Physicians are not relieved from criminal, civil and ethical responsibilities under the laws of their own countries.

**I. BASIC PRINCIPLES**

1. Biomedical research involving human subjects must conform to generally accepted scientific principles and should be based on adequately performed laboratory and animal experimentation and on a thorough knowledge of the scientific literature.

2. The design and performance of each experimental procedure involving human subjects should be clearly formulated in an experimental protocol which should be transmitted for consideration, comment and guidance to a specially appointed committee independent of the investigator and the sponsor provided that this independent committee is in conformity with the laws and regulations of the country in which the research experiment is performed.

3. Biomedical research involving human subjects should be conducted only by scientifically qualified persons and under the supervision of a clinically competent medical person. The responsibility for the human subject must always rest with a medically qualified person and never rest on the subject of research, even though the subject has given his or her consent.

4. Biomedical research involving human subjects cannot legitimately be carried out unless the importance of the objective is in proportion to the inherent risk to the subject.

5. Every biomedical research project involving human subjects should be preceded by careful assessment of predictable risks in comparison with foreseeable benefits to the subject or to others. Concern for the interests of the subject must always prevail over the interests of science and society.

6. The right of the research subject to safeguard his or her integrity must always be respected. Every precaution should be taken to respect the privacy of the subject and to minimize the impact of the study on the subject’s physical and mental integrity and on the personality of the subject.

7. Physicians should abstain from engaging in research projects involving human subjects unless they are satisfied that the hazards involved are believed to be predictable. Physicians should cease any investigation if the hazards are found to outweigh the potential benefits.

8. In publication of the results of his or her research, the physician is obliged to preserve the accuracy of the results. Reports of experimentation not in accordance with the principles laid down in this Declaration should not be accepted for publication.

9. In any research on human beings, each potential subject must be adequately informed of the aims, methods, anticipated benefits and potential hazards of the study and the discomfort it may entail. He or she should be informed that he or she is at liberty to abstain from participation in the study and that he or she is free to withdraw his or her consent to participation at any time. The physician should then obtain the subject’s freely-given informed consent, preferably in writing.

10. When obtaining informed consent for the research project the physician should be particularly cautious if the subject is in a dependent relationship to him or her or may consent under duress. In that case the informed consent should be obtained by a physician who is not engaged in the investigation and who is completely independent of this official relationship.

11. In case of legal incompetence, informed consent should be obtained from the legal guardian in accordance with national legislation. Where physical or mental incapacity makes it impossible to obtain informed consent, or when the subject is a minor, permission from the responsible relative replaces that of the subject in accordance with national legislation. Whenever the minor child is in fact able to give a consent, the minor’s consent must be obtained in addition to the consent of the minor’s legal guardian.

12. The research protocol should always contain a statement of the ethical considerations involved and should indicate that the principles enunciated in the present Declaration are complied with.

